**Fig. 2 Fig2:**
[figure not shown]
Current flow in anodal tDCS (verum stimulation). After a fade-in phase of 6 s, anodal tDCS is applied at an intensity of 2 mA for 10 min, ending in a fade-out phase of again 6 s

In the control group, a sham stimulation is applied, while the set-up is identical to the anodal tDCS group. The sham stimulation comprises identical fade-in and fade-out-periods (as anodal tDCS) with a short stimulation period of 20s in between, in which a current of 2 mA is applied. This procedure renders the blinding more effective. For the remaining “stimulation” time of 10 min, the tDCS-device performs impedance checks to verify proper electrode functioning and to ensure blinding of the investigator. The mean current applied over the sham stimulation period is below 2 μA and thus cannot modulate cortical excitability. The motor (cognitive) training is performed before and after the stimulation on five consecutive days in both tDCS groups.

The NeuroConn DC-stimulators have a study mode incorporated, which is essential for the double-blind procedure. Two-hundred five-digit codes are pre-programmed, which are either assigned to the verum or sham stimulation. The investigator is blinded to the link between the codes and the stimulation mode. In the process of randomization (see below), each participant is assigned to one of these codes, determining the intervention type (verum/sham). When the code is entered for tDCS application, the display remains identical in both modes during the entire stimulation. The fading of the current at the beginning of the sham stimulation was previously shown to be effective, as patients could not differentiate between verum and sham stimulation [10].

The allocation of codes is conducted via the online randomization service TENALEA (FormsVisions BV, Abcoude, the Netherlands), programmed by the Institute of Medical Statistics and Computational Biology of the University Hospital Cologne. Patients, investigators, and all other involved staff remain blinded for the entire duration of the clinical trial. In the rehabilitation centers, sealed envelopes are deposited for emergency unblinding, enabling the allocation of study arm for each stimulation code.

### Outcome measures

The primary outcome measure is the change of the total score of the Cologne Apraxia Screening (KAS [19];) achieved post-interventionally, compared to the patient’s baseline performance. The KAS is a reliable and valid screening tool [8], assessing bucco-facial and limb apraxia with two types of tasks (pantomime of tool use and imitation). The primary analysis is the comparison of the difference in the KAS-score changes between the two study arms (verum vs. sham stimulation) with a t-test in the ITT collective. If necessary, equivalent non-parametric methods are applied. The differences in KAS-score changes between follow-up and post-interventional assessments, as well as between follow-up and baseline assessments, are compared to evaluate a long-term effect. An analysis of variance (ANOVA) with the factor treatment and the co-factors age, KAS-score classification at baseline, and study site will investigate potential influences of the randomization strata on the treatment effect.

Secondary outcome measures are the changes in the additional neuropsychological and motor tests. Further apraxia assessments include the De Renzi test of actual object-use, the De Renzi imitation test, as well as the Goldenberg hand- and finger-imitation test. Moreover, aphasia is assessed by the short version of the Aphasia Check List (ACL-K). For general motor performance, the force of hand extension is assessed bimanually with the Medical Research Council (MRC) paresis scale, and the grip force is measured with a Vigorimeter (Martin Vigorimeter, medium-sized ball). Furthermore, the Action Research Arm Test (ARAT) is applied to both hands, and the Jebsen Taylor Hand Function Test (JTHFT) is applied to the ipsilesional (left) hand. To document the overall disability after stroke, we use the modified Ranking Scale (mRS).

As (cognitive) motor training, the ARAT, the De Renzi Imitation Test, and JTHFT are conducted before and after the stimulation sessions on the five interventional study visits (S1-S5 = T2-T6).

Additionally, the National Institutes of Health Stroke Scale (NIHSS), the Edinburgh Handedness Inventory (EHI), the Hospital Anxiety and Depression Scale (HADS), and the educational background are assessed at study inclusion.

Secondary outcome measures are assessed at the same time points as the primary outcome measures, i.e., at baseline, post-intervention, and follow-up, and are analyzed analogously to the primary outcome measures (see above).

To evaluate safety and tolerability of the stimulation, all participants receive a questionnaire after the five tDCS sessions about the occurrence of side / adverse effects of stimulation, their severity (1 = absent to 4 = severe), and the association of a putative adverse reaction with the test product (1 = none to 5 = definite). The questionnaire is based on a recommendation by Brunoni and colleagues to systematically assess the safety of tDCS [6]. For all (serious) adverse events ([S]AE), group comparisons are performed with Chi-square (or Fisher-exact) tests for the absolute occurrence as well as severity or causality. Further, to evaluate blinding efficacy, we ask the patients to ‘guess’ whether they received the ‘verum’ or the ‘sham’ stimulation (after all five stimulations have been performed). Further, patients are asked to provide a confidence rating for their guess regarding verum/sham tDCS.

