### Study description and study design

This multicenter study is an investigator-initiated, prospective randomized controlled trial (RCT) and follows a double-blinded (patient and investigator) study design with a parallel two-arm interventional model. As an intervention, we apply tDCS with CE-certified DC-Stimulators (NeuroConn, Ilmenau, Germany). In the context of motor rehabilitation after stroke, the clinical trial adheres to the German medical device law (Medizin-Produkte Gesetz, MPG; §23b).

We assume that the verum stimulation (anodal tDCS over the left parietal lobe) leads to a more significant improvement in apraxia severity than sham stimulation [1]. The primary endpoint is the difference in the total score of the Cologne Apraxia Screening (KAS [19]) between the post-interventional investigation and baseline. Thus, the null and alternative hypotheses are:
**H**_**0**_**:** The change of the motor-cognitive apraxic deficits (as assessed by the KAS) between the baseline assessment and the post-interventional assessment is the same in both treatment groups (verum tDCS and sham tDCS).**H**_**1**_**:** The change of the motor-cognitive apraxic deficits (as assessed by the KAS) between the baseline assessment and the post-interventional assessment is different in the verum tDCS group than in the sham tDCS group.

A pilot study following the identical interventional and training procedure was performed before this RCT [1]. Here, 20 apraxic patients showed a standard deviation (SD) of about 7 points in the comparison of the KAS-score between baseline and post-interventional assessment. The difference between the sham- and the verum-interventional group was 4.6 points. Based upon these data, a sample size of 50 per study arm is required to ensure a difference in effect of 4 points at an SD of 7 in a two-sample t-test at a level of significance of 0.05 and a power of 0.8. We added 10% for eventual non-parametric testing, leading to 55 patients per study arm or a total of 110 patients in the intention-to-treat (ITT) collective. Additional participants replace drop-outs that do not fulfill the ITT-criteria (i.e., drop-out before first stimulation).

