### Arms and interventions

After inclusion in the study, participants are randomized in the proportion 1:1 to both study arms, following a stratification by KAS-Score (i.e., apraxia severity; < 68 / ≥ 68 points), age (< 65 / ≥65 years), and site of investigation (Rehabilitationszentrum Godeshoehe e.V., Bonn / MediClin Fachklinik Rhein/Ruhr, Essen).

In the experimental group, anodal tDCS at an intensity of 2 mA is applied for 10 min on five consecutive days. The anodal rubber electrode (size: 5x7cm, 35cm^2^) is placed over the left PPC at position P3 of the 10/20 EEG system, the reference electrode (size: 5x10cm, 50cm^2^) is located supraorbitally on the right forehead. Electrodes are inserted into sponges and dampened with a saline solution to optimize electrode-skin-interface. To fix the electrodes, a rubber band is placed around the head in addition to the EEG cap.

To avoid sudden current changes, a fade-in and fade-out phase is applied, in which the current increases/decreases. Following the recommendation of the NeuroConn company, we ensured that the change of current is less than 0.5 mA per second. Therefore, we used fade-in and fade-out periods of 6 s duration each, resulting in a change of current of 0.5 mA/1.5 s (= 0.333 mA/s, see Fig. 2). During the stimulation, the patient is instructed to sit relaxed in a chair with eyes either closed or opened, without falling asleep (offline-stimulation).

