### Eligibility criteria

The criteria for inclusion in the study are defined as follows: (i) age between 18 and 90 years, (ii) LH ischemic stroke in the subacute/ chronic phase (here: > 10 days and < 180 days post-stroke), (iii) clinical presentation of apraxia in the Cologne Apraxia Screening (KAS; cut-off ≤76/ 80 points), and (iv) written informed consent by the patient or the legal guardian.

The criteria for exclusion of the study are defined as follows: (a) inability of the stroke patient to provide informed consent; in case of a legal guardian: the legal guardian is not available or declines consent; (b) pregnancy and breastfeeding; (c) patients with clinically manifest stroke before the index stroke; (d) malignant disease with affection of the central nervous system; (e) estimated life expectancy < 12 months; (f) current alcohol or drug addiction or other addictive disease (exception: nicotine); (g) current clinically manifest psychiatric disorders, such as schizophrenia or severe depressive episode; (h) epileptic seizure within the past two years; (i) intake of anti-epileptic drugs for prophylaxis of epileptic seizures; (j) continuous medication during the interventional phase with benzodiazepine or antipsychotics of high potential; (k) enrollment in other studies with brain stimulation in the period after the index stroke; (l) heart pacemaker; (m) electrodes for deep brain stimulation or other metal implants in the head; (n) craniectomy or cranial trepanation; (o) vulnerable skin lesions at planned electrode positions; and (p) poor motivation or cooperation.

In this study, LH stroke patients with apraxia are recruited during their inpatient stay in rehabilitation centers. The index stroke is diagnosed according to clinical standards (preferably including neuro-imaging with either cerebral computed tomography (CT) or cerebral magnetic resonance imaging (MRI)). If the patient provides written consent, the corresponding brain scans are obtained from the primary hospital and will be used for lesion mapping in the final reporting.

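### The primary t-test on KAS change makes no adjustment for baseline KAS or the stratification factors, so it is valid but probably conservative and less powerful than the same 110 patients allow

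*Protocol article*

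**What the plan says.** - **Endpoint** (Study description and study design): "The primary endpoint is the difference in the total score of the Cologne Apraxia Screening (KAS [19]) between the post-interventional investigation and baseline".
- **Primary test** (Outcome measures): the "difference in the KAS-score changes between the two study arms (verum vs. sham stimulation) with a t-test in the ITT collective", with a non-parametric equivalent if needed. No covariate is named.
- **Randomisation** (Arms and interventions): 1:1, with "stratification by KAS-Score (i.e., apraxia severity; < 68 / ≥ 68 points), age (< 65 / ≥65 years), and site of investigation".
- **Adjusted model** (Outcome measures): "An analysis of variance (ANOVA) with the factor treatment and the co-factors age, KAS-score classification at baseline, and study site". Its stated purpose is different from the primary comparison: it "will investigate potential influences of the randomization strata on the treatment effect".
- **Sample size** (Study description and study design): based on a "difference in effect of 4 points at an SD of 7 in a two-sample t-test at a level of significance of 0.05" and 80% power. This gives 50 per arm, raised by 10% to 55 per arm for possible non-parametric testing.
- **Entry range** (Eligibility criteria): KAS of 76 or less out of 80.

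**The concern.** Stratified randomisation forces the arms to be alike on KAS class, age class and site. If these factors predict KAS change, the treatment difference varies less from trial to trial than under simple randomisation. An unadjusted t-test does not register this: its error term still holds the between-stratum variance, so the standard error is too large. The design gains precision that the analysis does not use.

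The article gives two reasons to expect baseline KAS to predict change.

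- **Ceiling.** A patient entering at 76 can gain at most 80 − 76 = 4 points, which is the whole difference the trial is sized to detect. A patient entering much lower has no such limit.
- **Regression to the mean.** In Table 1 the only KAS before stimulation is the one at screening, so the score that qualifies the patient also serves as the baseline.

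The sponsor's own choice to stratify on KAS points the same way. At stake are power and the width of the confidence interval.

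**Working it through.** **1. The plan's own figure.** Inputs: difference 4, SD of change 7, two-sided 0.05, power 0.80. The exact noncentral t calculation gives 50 per arm (power 80.8%), and 50 × 1.10 = 55. The stated numbers reproduce. With 55 per arm, SE = 7 × √(2/55) = 1.335 and power is 84.4%, if the strata explain nothing.

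**2. What ANCOVA would do.** The article gives neither r nor the prognostic strength of the strata, so both are assumed. With equal baseline and post variances and a linear relation, the share of change-score variance explained by baseline is R² = (1 − r)/2. The adjusted SE is 7 × √(1 − R²) × √(2/55).

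| r (assumed) | R² | adjusted SE | 1.335 / adjusted SE |
|---|---|---|---|
| 0.5 | 0.25 | 1.156 | 1.15 |
| 0.8 | 0.10 | 1.266 | 1.05 |
| 0.9 | 0.05 | 1.301 | 1.03 |

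**3. Power with stratification taken into account.** The fair comparator is the t-test under stratified randomisation, whose true power exceeds 84.4% when baseline matters. Simulated trials of 110 patients, with KAS stratified at its median in blocks of 4 (both assumed) and 8,000 runs, gave the power figures below, with Monte Carlo error of about 0.4 points. A separate simulation, also with KAS-stratified blocks of 4, agreed on power to within about 1 point and gave the type I errors.

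| r (assumed) | t-test power | ANCOVA power | gain (points) | t-test type I error |
|---|---|---|---|---|
| 0.5 | 86.3% | 92.7% | 6.4 | about 3.4% |
| 0.7 | 85.1% | 89.1% | 4.0 | about 4.2% |
| 0.9 | 84.0% | 85.2% | 1.2 | about 5.0% |

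**4. Check on the mechanism.** For a normal baseline split at its median, the split captures 2/π = 0.637 of the baseline variance. At r = 0.5 the class explains 0.25 × 0.637 = 0.159 of the change-score variance. The true SD of the estimate is then 1.335 × √(1 − 0.159) = 1.224, while the t-test reports about 1.335. The critical value of 1.982 (108 df) acts like 1.982 × 1.335/1.224 = 2.16, a two-sided error of about 3.3%, in line with the simulated 3.4%.

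**5. All three strata.** A second set of simulations used eight strata, blocks of 4 (assumed) and 5,000 runs, and adjusted for the strata only.

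| R² of strata (assumed) | t-test type I error | t-test power | adjusted power |
|---|---|---|---|
| 0 | 5.2% | 84.2% | 83.7% |
| 0.10 | 4.3% | 84.6% | 86.7% |
| 0.20 | 2.8% | 87.2% | 91.5% |

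If the strata explain nothing, adjustment costs about 84.2 − 83.7 = 0.5 points. If they explain 10% or 20%, it gains 2.1 or 4.3 points.

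**The case against.** The strongest defence has four parts.

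- **The t-test is valid and the trial is sized for it.** This stands. Its type I error is at or below 5% apart from simulation noise, and 55 per arm gives about 84% power or more against a target of 80%. A reader might infer a false-positive risk or an underpowered trial; the article supports neither.
- **Baseline KAS is already used.** This stands in part. A reader might say that the test ignores baseline KAS, but the change score subtracts it. What is missing is covariate adjustment: subtraction fixes the baseline slope at 1, which under equal variances is less efficient than ANCOVA for any r below 1.
- **An adjusted ANOVA with all three strata is planned.** This narrows the point but does not remove it. The ANOVA is described apart from the primary analysis, has another purpose, and reduces KAS to two classes. It does not supply the primary estimate or p-value.
- **The size is unknown.** This stands. The article gives no r, no stratum differences and no baseline SD. The ceiling at 80 and the cut-off at 76 also make equal variances and linearity doubtful. The gain could be small.

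Two further inferences should be resisted. Comparing the ANCOVA power for r = 0.5 from the simple formula (92.9%) with 84.4% suggests a gain of 8.5 points, and invites translation into extra patients obtained at no cost. That comparator disregards the stratified randomisation and overstates the benefit. It is also tempting to add time since stroke as a covariate. The article gives only an eligibility window of more than 10 and fewer than 180 days, and nothing on whether time since stroke predicts KAS change.

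**Conclusion.** The point holds as one of efficiency. The article states the primary test, so this is a choice made rather than a detail left to the analysis plan, and a better choice is available from data already collected. For r between 0.5 and 0.9, with equal variances, linearity and KAS-stratified blocks, ANCOVA adds roughly 6 down to 1 percentage points of power, and the t-test's true type I error is about 3.4% to 5.0%. At r = 0.9 the difference is close to negligible. That the primary test omits adjustment is certain from the text; how much this costs is not. Stratification already limits imbalance between KAS classes, so only imbalance in baseline KAS within a class is left uncorrected.

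**What to change.** Before unblinding, define the primary analysis as an ANCOVA of post-interventional KAS (or KAS change; the treatment estimate is the same once baseline is a covariate) on treatment, with continuous baseline KAS, age and site. Report the adjusted difference in KAS points with its 95% confidence interval. Keep the unadjusted t-test, or its non-parametric equivalent, as a sensitivity analysis, and say which of the two applies and when, since the 10% inflation was added for that case. The ANOVA on the strata can stay in its present supporting role.

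The cost is a change of wording in the analysis section. The sample size of 110 need not change, and no further data are needed. If the strata prove uninformative, the expected loss is about 0.5 points of power.

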The primary collective for the analyses is the ITT collective, including all patients with the baseline KAS-score and the application of at least one stimulation. The secondary per-protocol (PP) collective includes all patients with a baseline and post-interventional KAS-score, plus the application of the verum or sham intervention according to the protocol, with the possibility of missing one stimulation, i.e., at least 4/5 stimulations must have been completed. The descriptive analysis will be conducted for the entire study cohort and both study groups. Two-sided statistical tests will be performed with the level of significance set to 0.05. The analysis of effectiveness will primarily be carried out in the ITT population “as randomized”. The PP population (at least 4/5 stimulations received) will be assessed for the sensitivity analysis. The analysis of safety will be conducted in the population “as treated” (at least 1/5 stimulations received).

Including screening, nine study visits are scheduled, eight of which are handled during the inpatient treatment in the neurological rehabilitation centers. The final, ninth (follow-up) visit can also take place at the patient’s home.

The primary outcome measures are collected at three time points: (1) baseline, i.e., in the week before stimulation, (2) post-intervention, i.e., in the week after stimulation, (3) follow-up, i.e., about three to four months after the stimulation. If patients assent, the neuropsychological and motor tests are recorded on video and re-evaluated for interrater-reliability. Please see the study flow chart Fig. 1 and Table 1 for the time points of the scheduled study visits and the respective motor and neuropsychological tests.

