**Fig. 1 Fig1:**
[figure not shown]
RAdiCS study flowchart. *will be escalated for drop-outs who did not receive a stimulation. Abbreviations: KAS=Kölner Apraxie Screening (Cologne Apraxia Screening), ACL-K=Short version of the Aphasia Check List, HADS=Hospital Anxiety and Depression Scale, MRC = Medical Research Council, mRS = modified Rankin Scale, NIHSS=National Institutes of Health Stroke Scale, ARAT = Action Research Arm Test, JTHFT = Jebsen Taylor Hand Function Test. For a list of the applied tests at a given time point, please, see Table 1

**Table 1 Tab1:** List of applied tests at a given time point (T0-T8)

			Stimulation						
			S1	S2	S3	S4	S5		
Time point	T0	T1	T2	T3	T4	T5	T6	T7	T8
Method									
Edinburgh Handedness Inventory (EHI)	X								
Hospital Anxiety and Depression Scale (HADS)	X								
Aphasia Check List - Short version (ACL-K)	X							X	X
Cologne Apraxia Screening (KAS)	X							X	X
National Institutes of Health Stroke Scale (NIHSS)		X							
Goldenberg hand- and finger-imitation test		X						X	X
De Renzi test of actual object-use		X						X	X
De Renzi imitation test			XX	XX	XX	XX	XX		X
Action Research Arm Test (ARAT)			XX	XX	XX	XX	XX		X
Jebsen Taylor Hand Function Test (JTHFT)		4X	XX	XX	XX	XX	XX		4X
Modified Rankin Scale (mRS)		X						X	X
Medical Research Council (MRC)		X						X	X
Vigorimeter (for grip force)		X						X	X

T0 = Screening, T1 = Baseline assessment, T2-T6 = assessments at the stimulation sessions (S1-S5), T7 = Post-interventional assessment, T8 = Follow-up assessment

X = single application of the test, XX = application before and after the stimulation (verum or sham tDCS), 4X = 3 times of training and measurement of the 4th trial

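### The mRS and MRC grades inherit the KAS change-score test; an ordinal model adjusted for the T1 grade would use the same data better, with T8 read as the longer-term disability result

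*Protocol article*

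**What the plan says.** In the protocol article, Outcome measures, the form of the secondary outcomes is fixed: "Secondary outcome measures are the changes in the additional neuropsychological and motor tests". They are measured at the same time points as the primary outcome "and are analyzed analogously to the primary outcome measures (see above").

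The rule referred to has four parts:
- The change in KAS from baseline to the post-interventional visit is compared between arms "with a t-test in the ITT collective".
- "If necessary, equivalent non-parametric methods are applied".
- The changes from post-intervention to follow-up, "as well as between follow-up and baseline assessments, are compared to evaluate a long-term effect".
- An ANOVA takes treatment with the stratification factors: age, KAS class and site.

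The mRS is the measure named for overall disability, and the MRC grade is the paresis measure. Neither is exempted from the rule. Table 1 schedules both at T1, T7 and T8.

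Under Study description and study design, T1 falls in the week before stimulation and T7 in the week after. T8 follows about three to four months after stimulation. Of the nine visits, "eight of which are handled during the inpatient treatment in the neurological rehabilitation centers"; the ninth (T8) may take place at the patient's home.

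**The concern.** One template written for an 80-point score is applied to coarse ordered grades. Two features fit badly.

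First, a difference of grades counts every step as equal and fixes the weight on the baseline grade at one. None of the planned analyses adjusts for the baseline grade of the outcome itself: the ANOVA adjusts for age, KAS class and site only. The rank-test option does not change this, because it ranks the same differences.

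Second, carrying over the KAS order puts T7 minus T1 first. Five stimulation days, with T1 up to a week before and T7 up to a week after, make an interval of about one to three weeks within one inpatient stay. A modest effect on a global disability grade would be hard to detect there.

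At stake is how the disability result is read. The abstract's Perspective hopes for less impact of apraxia on daily living and long-term outcome, and the mRS is the listed outcome that grades overall disability. A null at T7 could be taken as absence of functional benefit, while the T8 grades are analysed less efficiently than they could be.

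**Working it through.** **1. The plan's own figure.** Inputs from Study description and study design: difference 4, SD 7, two-sided alpha 0.05, power 0.80. The normal approximation gives n = 2 × (1.960 + 0.842)² × 7² / 4² = 48.1, so 49 per arm. The noncentral t calculation gives 49.05, so 50. Then 50 × 1.10 = 55 per arm. The stated size reproduces, but it concerns the KAS only; the mRS is not powered.

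**2. What 55 per arm can detect at T7.** For 80% power the t-test needs a standardised difference of 0.54. To translate this to the mRS, assume no missing data, 2% worsening by one grade, and all others unchanged or one grade better (6,000 simulated trials per row):

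| Improved, sham vs verum | t-test on change | Mann-Whitney on change |
|---|---|---|
| 5% vs 10% | 0.13 | 0.14 |
| 10% vs 15% | 0.11 | 0.11 |
| 5% vs 15% | 0.34 | 0.35 |
| 10% vs 20% | 0.26 | 0.26 |
| 20% vs 30% | 0.20 | 0.21 |
| 5% vs 25% | 0.79 | 0.80 |
| 10% vs 30% | 0.70 | 0.72 |
| 20% vs 40% | 0.58 | 0.60 |

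Differences of 5 to 10 points give power of about 0.11 to 0.35. Power near 0.80 needs about 20 to 25 points, and slightly more when 20% improve under sham (20% vs 45%: 0.76 and 0.78). With no effect, both tests reject in about 0.04 to 0.05 of trials. The rank test gains at most about 2 points.

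**3. T8: test on change against adjustment for T1.** Correlated latent severities at T1 and T8 were cut into mRS grades, with treatment as a common odds ratio (OR) at T8 and 55 per arm. Three runs used different assumed grade distributions (A and C 400 trials per cell, B 600). The standard error of a power estimate is at most √(0.25/400) = 0.025 (B: 0.020).

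| Run | OR | Correlation | t-test on change | Proportional odds adjusted for T1 | Gain, points |
|---|---|---|---|---|---|
| A | 2.0 | 0.3 / 0.5 / 0.7 | 0.44 / 0.56 / 0.76 | 0.53 / 0.65 / 0.77 | 9 / 9 / 1 |
| A | 2.5 | 0.3 / 0.5 / 0.7 | 0.70 / 0.82 / 0.91 | 0.78 / 0.86 / 0.93 | 8 / 4 / 2 |
| B | 2.0 | 0.3 / 0.5 / 0.7 | 0.45 / 0.54 / 0.77 | 0.59 / 0.61 / 0.80 | 14 / 7 / 3 |
| B | 2.5 | 0.3 / 0.5 / 0.7 | 0.66 / 0.77 / 0.92 | 0.80 / 0.85 / 0.93 | 14 / 8 / 1 |
| C | 2.0 | 0.3 / 0.5 / 0.7 / 0.85 | 0.43 / 0.57 / 0.72 / 0.94 | 0.56 / 0.65 / 0.74 / 0.95 | 13 / 8 / 2 / 1 |

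Gains of 1 to 3 points are within simulation error. At OR 1.5 in run C, power was about 0.19 to 0.51 for the t-test and 0.23 to 0.49 for the ordinal model over correlations 0.3 to 0.85, so there was little or no gain. In run B at OR 2.0, a Mann-Whitney test on change had 0.46 / 0.54 / 0.75, the same as the t-test within error.

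**4. Where the gain comes from.** Run C also fitted an ordinary linear model of the T8 grade adjusted for T1. At OR 2.0 its power was 0.54 / 0.61 / 0.73 / 0.93. At correlation 0.3, adjustment alone gives 11 of the 13 points (0.43 to 0.54) and the ordinal model the other 2. At 0.5 the split is 4 and 4.

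The direction is as expected. With equal variances, a change score has variance 2σ²(1 − ρ) and an adjusted score σ²(1 − ρ²), a ratio of (1 + ρ)/2. That is 0.65 at ρ = 0.3, 0.85 at 0.7 and 0.925 at 0.85, so the advantage fades as the correlation rises.

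**5. Caveat.** In run B the likelihood-ratio test of the ordinal model was slightly liberal (type I error 0.06 to 0.07, against 0.05 to 0.06 for the comparison). A little of the gain is therefore not real.

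**The case against.** The strongest case against is that little harm follows. The same rule that brings in the t-test also brings in a non-parametric option and the two comparisons with follow-up. Disability at three to four months is thus already collected and compared, at a visit that may be at home. The article never calls T7 the main mRS time point; that is inferred from the order of the KAS analysis. The simulations generate data under proportional odds, which favours the proposed model, and the grade distributions, correlations and odds ratios are all assumed. The mRS is one of several unpowered secondary outcomes in a condensed article, and an analysis plan not shown may refine the method.

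Most of this stands and limits the point. A reader might infer that the disability result is a near-certain null from a visit that cannot show change. The article does not support that: it gives no mRS distribution, and assumed T7 effects gave power anywhere from 0.11 to about 0.80. Low power at T7 would come from the coarse scale and short interval, not from the t-test. Nor is the mRS the test of the trial's stated aim, which is recovery of apraxia; daily living appears as a hoped-for consequence.

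What does not stand is that the matter is simply left open. The article states a rule for all secondary outcomes, and that rule contains no adjustment for the outcome's own baseline grade.

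**Conclusion.** The point holds as a modest one about efficiency and interpretability. The planned test on change is valid, but for the mRS and MRC grades a better analysis of data already scheduled is available. For the T8 mRS the gain is roughly 0 to 15 points of power: most at a T1-T8 correlation of about 0.3, almost none at 0.85. Where it is large, it comes mainly from adjusting for T1 rather than from the ordinal form. This rests on 55 per arm, no missing data, assumed grade distributions and a proportional-odds effect of about 2.0 to 2.5; at 1.5 the gain is smaller or absent. No calculation was made for the MRC grade; it is included because the same rule applies to the same kind of scale. It does not follow that the t-test is invalid or that disability is assessed only in hospital.

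**What to change.** Exempt the mRS and the MRC grade from the analogous-analysis sentence. For each, replace the unadjusted test on change with a proportional-odds model of the grade at T7 and, separately, at T8, with treatment and the T1 grade as terms. State that the T8 mRS is interpreted as the longer-term disability result, and still report T7. If the unpublished analysis plan already does this, a sentence saying so is enough.

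The cost is wording only, since both grades are already scheduled at T1, T7 and T8. The small downside is that the effect becomes a common odds ratio under a proportional-odds assumption rather than a mean difference.
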